# Evaluation of the effect of vitamin D supplementation on spermatogram, seminal and serum levels of oxidative stress indices in asthenospermia infertile men: a study protocol for a triple-blind, randomized controlled trial

**DOI:** 10.1186/s12937-021-00711-7

**Published:** 2021-06-02

**Keywords:** Vitamin D, Oxidative stress, Infertile men, Idiopathic asthenospermia, Semen quality, Sex hormones

## Abstract

**Background:**

It is suggested that vitamin D may have a beneficial role in male reproduction. The male reproductive system is a target tissue for vitamin D. This study will aim to evaluate the effects of vitamin D supplementation on sperm parameters, seminal and serum levels of oxidative stress and serum endocrine factors in asthenospermia infertile men.

**Methods/design:**

This randomized, triple-blind, placebo-controlled clinical trial will be conducted on 86 infertile men with idiopathic asthenozoospermia (the mobility of sperm < 40% and rapid progressive sperm motility < 32%), with serum levels of vitamin D less than 30 ng / ml in the “Infertility Clinic of Ahvaz Jahad daneshgahi”, Iran.

**Main outcomes measure (s):**

Demographic data, dietary intake, physical activity, sun exposure, anthropometric indices, serum and seminal levels of MDA (Malondialdehyde), 8-hydroxy-2- Dioxy Guanosine (8-OHDG), Total Antioxidant Capacity (TAC) and calcium, sperm DNA fragmentation index (DFI), serum 25-OHD, luteinizing hormone (LH), follicle-stimulating hormone (FSH), total testosterone (T), estradiol (E2), sex hormone-binding globulin (SHBG), free androgen index (FAI = T/SHBG. 100), T/LH and T/E2 ratios, prolactin (PRO), parathyroid hormone (PTH), osteocalcin (OCN), phosphorus and sperm parameters.

**Discussion:**

The deficiency of vitamin D as an antioxidant is common all over the world. Numerous observational studies have shown a positive association between vitamin D levels and semen quality. However, few clinical studies have been conducted in this area. So considering with the high prevalence of this antioxidant deficiency specifically in infertile men, it seems that the supplementation of vitamin D in infertile men with insufficient levels or deficiency may improve the status of oxidative stress and thereby may affect sperm parameters and endocrine factors involved in male fertility.

**Trial registration:**

Iran Clinical Trials Registry, ID: IRCT20151128025274N4, registered on 28 March 2018.

**Supplementary Information:**

The online version contains supplementary material available at 10.1186/s12937-021-00711-7.

## Introduction

Infertility is defined as the inability to have a child after at least 1 y of marriage without using any preventive method (WHO). About 15% of couples across the world suffer from infertility [1]. The prevalence of infertility is 24.9% among Iranian couples, which is greater than the global average [2]. It is indicated that about half of the causes of infertility is attributed to the male partner [1]. Nineteen percent of infertile cases have asthenospermia, the impaired sperm motility. Persistent poor motility predicts failure in fertilization [1].

The oxidative stress (OS) caused by increased production of reactive oxygen species (ROS) in semen have been suggested as an important causative factor in the etiology of asthenospermia [3]. Spermatozoa were the first cells in which the production of ROS was reported. Macleod (1943) reported that the incubation of spermatozoa at high oxygen pressures slowed down the sperm motility due to increased production of H_2_O_2_ [4]. It should be noted that ROS, at low physiological concentrations, are required for maturation, capacitation, hyper activation of sperm, the acrosome reaction, and fertilization [5]. However, the excessive production of ROS may lead to serious damage to the cell function [6]. Immature and abnormal spermatozoa, along with positive peroxidase leukocytes (neutrophils and macrophages) are considered as two major endogenous sources of continuous ROS production [7]. Researches showed that ROS and their metabolites can attack Deoxyribonucleic acid (DNA), lipids, and proteins and may lead to alter enzymatic systems; produce irreparable alterations; cause cell death and ultimately impair the semen parameters associated with male infertility. It is known that spermatozoa are susceptible to oxidative damage as their plasma membranes are rich in polyunsaturated fatty acids and have low concentrations of scavenging enzymes [8]. Studies have shown that the concentration of malondialdehyde (MDA), which is an indicator of lipid peroxidation, is twice as high in infertile men with asthenospermic and oligoasthenospermic infertility compared with men with normospermic [9].

Many researchers suggested that measuring 8-hydroxydeoxyguanosine (8-OHdG), a product of DNA oxidation, in sperm and seminal fluid can be a proper and direct indicator of oxidative damage of sperm DNA [10]. DNA damage by active oxygen species can lead to the transmission of defective paternal DNA to the fetus. One of the common methods to measure the damage on sperm DNA is the SCD test in which the amount of denatured DNA is determined. The amount of denatured DNA is evaluated using DNA fragmentation index (DFI). Studies have shown that the DFI levels above 27% are associated with not only the increased fertility failure but also the failure of assisted reproductive techniques [11, 12]. In addition, the inflammation caused by free radicals can reduce the production of testosterone (T) and Luteinizing hormone (LH) and thereby affect fertility [13–15]. There are series of enzymatic antioxidants and low molecular weight antioxidant compounds in seminal plasma and sperm, which can protect the sperm against the ROS damage [10, 16, 17]. Studies found that the antioxidant capacity of seminal fluid in infertile men is lower than fertile men [18, 19].

There are several treatment approaches for infertility including surgery, prescription of medications for the production and mobility of sperm and the artificial fertility, which the most are expensive. Moreover, there are some alternative cost-effective methods such as using food supplements with antioxidant properties, reported to increase the sperm count and motility [20–22].

Vitamin D is considered as an important micronutrient with many biological effects. Vitamin D deficiency is the epidemic concern of modern age and the most common nutritional deficiency worldwide [23, 24]. The expression of vitamin D receptors (CYP2R1, CYP27B1 and CYP24A1) and enzymes involved in the metabolism and activation of vitamin D in testicles specifically in leydig cells, in epididymis, seminal vesicles, prostate and spinal cord and the head of sperm indicate the importance of the role of vitamin D in fertility and reproduction in men [22]. According to evidence, vitamin D levels are greater in fertile men than in infertile men. Also, there is an association between vitamin D deficiency and low sperm quality in infertile men according to several studies [25–27]. In addition, animal studies showed that vitamin D deficiency is linked to an increase in sperm DNA fragmentation [28]. Deng XL et al. showed that the 3 months supplementation with Vitamin D and calcium in oligo-asthenozoospermia infertile men significantly increased sperm progressive motility and rate of pregnancy in the intervention group [29]. In contrast Blomberg Jensen et al. [30] and Amini et al. [31] found no significant differences in sperm parameters between two groups post intervention in the RCTs.

Furthermore, the impact of vitamin D deficiency on serum levels of testicular hormones have been assessed by several animal, observational and interventional studies with controversial results regarding with clear relationship between vitamin D status and testicular hormone production [32–49].

### Objectives and hypotheses of the study

Based on the evidence indicating that the expression of vitamin D receptors and enzymes are involved in the metabolism of vitamin D in genital and male sperm, it is hypothesized that vitamin D may have potential role in spermatogenesis, sperm maturation, endocrine functions and thereby in improvement of male fertility. Moreover, regarding with the role of OS in the etiology of poor semen quality and male infertility, and also considering the antioxidant role of vitamin D and high prevalence of vitamin D deficiency in Iran, we propose that vitamin D supplementation may improve the OS, sperm parameters such as sperm motility and endocrine factors involved in male fertility. To the best of our knowledge, in the most studies conducted on the effects of antioxidants on infertility, some antioxidants such as vitamin E, selenium and vitamin C were used as supplements. There are only few clinical trials with controversial results evaluated the effects of vitamin D supplementation on male infertility. Furthermore, most of these studies used the adjunctive supplementation of Vitamin D and calcium. Also, there is no clinical study has examined the effect of vitamin D supplementation on OS markers in men with asthenospermia and insufficient vitamin D levels or vitamin D deficiency. Therefore, it is suggested that further clinical studies are needed in this field. So, the main objective of this study is to evaluate the effects of vitamin D supplementation on sperm parameters, seminal and serum levels of OS markers and also serum endocrine factors in asthenospermia infertile men.

## Methods/design

### Study subjects

This trial will be conducted on 86 infertile men with idiopathic asthenozoospermia (the mobility of sperm < 40% and rapid progressive sperm motility < 32% [50], and with serum vitamin D levels < 30 ng / ml, who report inability to have a child after at least 1 y of marriage without using any preventive methods and with normal fertile female partner in the Infertility Clinic of Ahvaz Jahad daneshgahi, Iran. The further inclusion criteria are listed in Table 1.

**Table 1 Tab1:** Inclusion and exclusion criteria

Inclusion	
•Men aged 20 to 50 years	
•Idiopathic asthenozoospermia (the mobility of sperm < 40% and rapid progressive sperm motility < 32%	
•Serum vitamin D levels < 30 ng / ml	
•Access to the infertility clinic of Ahvaz Jahad daneshgahi, Iran	
•Inability to have a child after at least 1 y of marriage without using any preventive methods	
•Normal fertile female partner	
•No history (≤ 12 weeks) of medical therapy	
•Not having a history of epididymo-orchitis, prostatitis, genital trauma, testicular torsion, inguinal or genital surgery, urinary tract infection, or previous hormonal therapy, another genital disease (cryptorchidism, current genital inflammation or varicocele), a recent history of sexually transmitted infection, hepatobiliary disease and renal insufficiency, severe general or central nervous system disease and endocrinopathy, using cytotoxic medications, immunosuppressant, anticonvulsants, androgens, antiandrogens	
•No smoking, drug or alcohol abuse, and	
•No occupational and environmental exposure to possible reproductive toxins	
•Body mass index of < 30 kg/m^2^	
Exclusion	
• Have any acute illness	
• Use less than 90% of the prescript supplement	
• Would like to leave the study personally	
• Participate in another study	
• Immigrate	
• Not available for following-up	

### Design

This study is a randomized, triple-blind, placebo-controlled clinical trial. There will be four study phases consisting of baseline phase I “enrolment”, baseline phase II “randomization and allocation”, treatment and follow up over 12 weeks (Fig. 1). Participants will be randomly allocated into two groups of either receiving 4000 IU/d [51, 52] vitamin D3, or a matched placebo. Participants, the researchers, and statistical counselor will be blinded in terms of the type of intervention throughout the trial. All visits will be held in the “Infertility Clinic of Ahvaz Jahad daneshgahi”, Iran during the day.

**Fig. 1 Fig1:**
[figure not shown]
Flow diagram of the study

### Primary aim

The primary aim of the present study is to improve serum levels of 25OHD3 through vitamin D3 supplementation in order to evaluate its effects on fertility in infertile men. The compliance of subjects will be monitored by counting the remaining supplements. The subjects who may not use greater than 90% of the supplements will be excluded. We expect that the drop-out rates will be high in this study. Therefore, we would consider a 25% attrition rate for each group of study.

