### Withdrawal of participants

Participants who may withdraw prior to the randomization (during baseline phases I and II), will be replaced with new eligible participants. The exclusion criteria in this study would be as: have any acute illness, use less than 90% of the prescript supplement, would like to leave the study for personal reasons, participate in another study, immigrate and not available for following-up.

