### Semen and blood samples

Semen samples will be obtained after 3 days of sexual abstinence. All semen samples will be held at 37C until the liquefaction. The sperm quality parameters such as ejaculate volume, total sperm count, sperm concentration, motility grade and sperm with normal morphology (%) will be assessed according to the WHO criteria [55]. The other biochemical analysis such as seminal levels of oxidative stress markers including malondialdehyde (MDA), 8-hydroxy-2- Dioxy Guanosine (8-OHDG) and total antioxidant capacity (TAC) and calcium will also be analyzed. Sperm DNA fragmentation will be assessed using sperm chromatin dispersion (SCD) method [11, 12].

Moreover, 10 cc of intravenous blood samples will be collected from patients to analyze biochemical parameters including 25 hydroxyvitamin D (25-OHD), oxidative stress index (TAC and MDA) and 8-OHDG, Sex hormones (total testosterone, estradiol (E2), luteinizing hormone (LH), follicle-stimulating hormone (FSH), sex hormone-binding globulin (SHBG), prolactin), parathyroid hormone (PTH), osteocalcin, calcium, and phosphorus.

The measurement of serum calcium and phosphorus and seminal calcium will be done using calorimetric method. Seminal and serum levels of vitamin D, TAC, MDA, 8-OHDG, PTH, osteocalcin, Testosterone, E2, SHBG, luteinizing hormone (LH), follicle-stimulating hormone (FSH), and prolactin will be assessed by enzyme-linked immunosorbent assay (ELISA).

During Baseline Phase II, the participants will be excluded if they have:
Body mass index (BMI) > 30 kg/m^2^Normal semen samples analysis for sperm motility (the mobility of sperm > 40% and rapid progressive sperm motility> 32%)Sufficient serum levels of 25OHD levels (> 30 ng / ml)Intense physical activity (> 3000 met/cal/week)

In visit 3 patients will be randomly allocated to either group A, receiving 4000 IU/d [51, 52] vitamin D3, or group B, receiving a matched placebo for 12 weeks (Randomization and blinding method described above).

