### Statistical analysis

Intention-to-treat (ITT) and per-protocol (PP) populations will be used in the analysis. The ITT population consists of all individuals who will be randomized, whereas the PP population consists of all participants who complete the 12-week intervention. All data will be analyzed using SPSS (Version 22; SPSS Inc., Chicago, IL). Results will be expressed as mean ± SD and frequency and (percentage) for quantitative and qualitative variables respectively. The normal distribution of variables will be tested and confirmed by Kolmogorov-Smirnov test. The baseline differences of mean values between groups will be tested using independent sample t-test or Mann-Whitney U test for normal and non- normal distribution variables respectively. Analysis of covariance (ANCOVA) will be used to identify any differences between the two groups at the end of study, adjusting for baseline values and covariates (such as BMI, age, dietary intake including dietary calorie, calcium, F, selenium, vitamin C, E, A, D and zinc, physical activity, sun exposure, season, serum vitamin d, PTH and calcium). The comparison of mean values within groups pre- and post-intervention will be done by paired sample t tests and Wilcoxon signed-rank test as nonparametric alternatives for normal and non- normal distribution variables respectively. Differences will be considered statistically significant at *P* < 0.05.

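### Men below 90% adherence are excluded after randomisation, which conflicts with the stated ITT and per-protocol sets

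*Protocol article*

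**What the plan says.** The adherence rule appears in three places in the protocol article:

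- **Primary aim:** "The subjects who may not use greater than 90% of the supplements will be excluded". The measure is given just before it: "The compliance of subjects will be monitored by counting the remaining supplements". The same paragraph then goes on to expect high drop-out and to allow 25% attrition per group.
- **Table 1 (Study subjects), exclusion list:** "Use less than 90% of the prescript supplement", next to "Have any acute illness".
- **Withdrawal of participants:** the criteria include "have any acute illness, use less than 90% of the prescript supplement, would like to leave the study for personal reasons", followed by joining another study, emigration and being unavailable for follow-up. Only withdrawals before randomisation are replaced: "Participants who may withdraw prior to the randomization (during baseline phases I and II), will be replaced with new eligible participants".

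On timing, Semen and blood samples states: "In visit 3 patients will be randomly allocated to either group A". The treatment phase, with one pill a day for 12 weeks, comes after that, and outcome samples are taken at visit 5.

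The analysis sets are defined under Statistical analysis: "The ITT population consists of all individuals who will be randomized, whereas the PP population consists of all participants who complete the 12-week intervention". Both sets are to be used, and neither is named as primary.

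**The concern.** A pill count exists only once pills have been dispensed, so exclusion for low adherence acts on men already randomised. An ITT set of all randomised men has no room for such a rule. The per-protocol set, where a 90% threshold would normally sit, has none. The threshold is therefore attached to the trial as a whole and to neither analysis set.

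The surrounding text suggests that these men are counted as lost. The Primary aim section moves directly from the exclusion to the attrition allowance, and the withdrawal list puts low adherence beside loss to follow-up. If excluded men provide no visit 5 sample, the ANCOVA of end-of-study values has no observed outcome for them. The comparison labelled ITT would then rest on men selected by what they did after allocation. Randomisation does not protect that comparison, and it answers a different question from the effect in all men assigned the supplement. ITT and per protocol would also no longer serve as a useful check on each other.

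**Working it through.** **1. The rules side by side.** The course is 12 × 7 = 84 pills, and 84 × 0.90 = 75.6. A man who misses 8 has taken 76 (90.5%) and stays in. A man who misses 9 has taken 75 (89.3%) and is excluded. No whole number of pills equals exactly 90%, so the slightly different wordings (not greater than 90%, less than 90%) give the same result.

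Take a man who takes 75 pills and attends at week 12:

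| Section | His status |
|---|---|
| Primary aim; Table 1; Withdrawal of participants | Excluded |
| Statistical analysis, ITT | Included (randomised) |
| Statistical analysis, per protocol | Included (completed 12 weeks; no threshold) |

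The contradiction needs no assumption about follow-up.

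**2. The plan's own figures.** The Sample size section gives two-sided alpha 0.05, 90% power, 34 per group, 25% attrition and 43 per group. The 43 is reproduced as 34 × 1.25 = 42.5, rounded up. (Dividing by 0.75 would give 45.3, so 46; that is a separate matter.) The 34 cannot be reproduced directly, because no mean difference or SD is stated. Solving the article's formula for the standardised difference gives

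d = √[2 × (1.960 + 1.282)² / 34] ≈ 0.79.

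This is a back-calculation, not a figure in the article.

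**3. How many men.** The planned attrition is 0.25 × 86 = 21.5 men, leaving 43 × 0.75 = 32.25 per group. It covers every reason for loss, not only low adherence.

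**4. Effect in all randomised men.** Assume that 25% are non-adherent, that adherent men have d = 0.79, and that non-adherent men keep a fraction f of that effect. The all-randomised effect is d × [1 − 0.25 × (1 − f)]. Power is for two-sided alpha 0.05 with all 43 per group analysed.

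| f (assumed) | Effect in all randomised | Power, 43 per group |
|---|---|---|
| 1 | 0.79 | 95% |
| 0.5 | 0.69 | 89% |
| 0 | 0.59 | 78% |

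If instead about 32 per group are analysed at 0.79, power is about 88%. The choice of set therefore affects both the quantity estimated and the power.

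**5. Acute illness.** This criterion is in Table 1 and in Withdrawal of participants, but not in Primary aim. The enrolment section applies Table 1 at visit 1, so it may be a screening criterion. Its place in the withdrawal list, among on-treatment events, points to the treatment period. The text does not settle which is meant.

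**The case against.** The strongest reply is that the article commits to ITT as everyone randomised, and that excluded may only mean left out of one analysis. It describes no clinic visit between visit 4 and visit 5, so a final pill count would naturally fall at visit 5, when blood and semen are collected. Visit 5 carries no adherence condition. Men below 90% may therefore have outcome data. This stands, and it makes the loss of the ITT comparison conditional. It does not remove the contradiction. The rule cannot be read as simply the per-protocol definition, because that set is defined by completion without a threshold. The daily phone or message contact about compliance also means that non-adherence could come to light before visit 5.

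A second reply concerns size, and it also stands. Missing 9 of 84 pills triggers the rule, so assuming no benefit in every excluded man is an extreme bound. Putting the whole 25% down to non-adherence ignores the other listed reasons for loss. Matched, coded containers and triple blinding give no ground for assuming that exclusion differs between arms.

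Thirdly, the full protocol or an analysis plan may spell out follow-up of excluded men and the handling of missing data. For that reason the absence of a missing-data method is not part of this point. The point rests on rules that the article does state.

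**Conclusion.** The point holds as a conflict between stated rules. Three sections exclude men on adherence measured after randomisation, and the analysis section defines ITT and per protocol in ways that keep those men. Applied as written, the exclusion moves the ITT comparison toward retained adherent men.

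The size is illustrative only. With 25% non-adherent, the all-randomised effect lies between 0.79 and 0.59, depending on how much of the effect these men keep. This rests on the back-calculated 0.79 and on attributing all attrition to non-adherence, so the lower end is an extreme.

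A reader might infer three stronger things that the article does not support:

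- **That ITT and per protocol are bound to contain the same men.** No section says that excluded men miss visit 5.
- **That acute illness is necessarily a post-randomisation exclusion.** It can also be known at screening.
- **That a bias of a particular size between arms follows.** This would need unequal exclusion rates and a prognostic difference, and the article gives no figure for either.

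**What to change.** - Remove low adherence as a reason for exclusion from the trial in Table 1, Primary aim and Withdrawal of participants.
- State that visit 5 blood and semen are sought from every randomised man, however much supplement he took.
- Reconcile Table 1 and Withdrawal of participants on whether acute illness is a screening criterion, an on-treatment event or both. It need not be deleted as an eligibility criterion. State that a man who falls acutely ill after randomisation stays in follow-up and in the ITT set. Whether he continues the supplement is a clinical matter on which this point takes no position.
- Name ITT as the primary analysis.
- Define per protocol as 12-week completers who took at least 90% of the supplement.

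The cost is revised wording and some effort to bring back men who stop. The ITT estimate may be smaller than one in adherent men. Recruitment began in April 2018 and was expected to finish in September 2021, so the change cannot recover visit 5 samples from men already excluded. Their number should be reported by arm and reason.
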